### Primary outcomes

The primary outcome is ED psychopathology, measured using the global score from the EDE-Q^13^ over the past 28 days. The global score can range from 0 to 6, and higher scores indicate greater psychopathology. This measure has adequate psychometric properties^30 31^ and is widely used to assess and monitor EDs in clinical practice and treatment outcome studies.

### Secondary outcomes

The secondary outcomes include behavioural indicators of the ED, impairment caused by the ED, general negative emotion, self-harm and hope.

We will examine the five behavioural items on the ED15, used at each session. The ED15 is a 15-item questionnaire that assesses behaviours and cognitions during the previous week.^29^ Six items assess weight and shape concerns (eg, “felt distressed about my body shape”) and four assess eating concerns (eg, “worried about losing control over eating”) on a seven-point Likert scale (0=not at all to 6=all the time). Higher ratings indicate higher levels of psychopathology. Five additional questions assess the frequency of disordered eating behaviours (binge eating, vomiting, laxatives, excessive exercise, restriction), but these do not contribute to those two scales. The reliability and validity of the ED15 have been supported.^32^

The 16-item Clinical Impairment Assessment Questionnaire (CIA)^33^ is a self-report measure of psychosocial impairment in the past 28 days attributed to experiencing an ED. Impact on areas of functioning such as mood and self-perception, cognitive functioning, work performance and interpersonal functioning is measured on a 4-point Likert scale (0=not at all to 3=a lot). The CIA correlates with ED psychopathology and has good discriminant^34^ and predictive validity.^35^

The total score of the 21-item version of the Depression Anxiety Stress Scale (DASS-21)^36^ will be used, where factor analysis indicates that a general factor of psychological distress or general negative emotion exists.^37^ Participants rate the extent to which a statement applies to them in the past week on a 4-point Likert scale (0=never, 3=almost always). Higher scores indicate higher severity of symptoms. The DASS-21 has sound psychometric properties, including internal consistency, convergent validity and discriminant validity.^38^

Section I of the Inventory of Statements About Self-Injury (ISAS)^39^ assessing behavioural items will be used to measure self-harm. The ISAS has been shown to have satisfactory psychometric properties, including test-retest reliability.^39 40^ Seven items assess type and frequency of self-harm behaviours.

The 8-item Adult Hope Scale^41^ will be used to measure dispositional hope. Each item is scored on an 8-point Likert scale, ranging from ‘definitely false’ to ‘definitely true’. Higher scores represent higher levels of hope. As well as a total score, two subscales can be identified that measure pathway thinking (eg, I can think of many ways to get out of a jam) and agency thinking (eg, I energetically pursue my goals). The scale has been found to be valid and reliable in adults.^42^

### Other measures

Other measures include demographics, functions of self-harm, healthcare use, and feedback about the service (aspects least and most liked), and acceptability as indicated by the number of sessions completed and premature cessation of therapy (drop-out). Demographic information will include ED diagnosis, age, duration of the ED, cultural identity, previous mental health treatment, gender, socioeconomic status, and one item assessing importance of change and ability to change. The functions of self-harm will be assessed only at baseline to inform treatment, using Section II of the ISAS,^43^ consisting of 39 items scored on a 3-point scale: not relevant, somewhat relevant and very relevant. There are 13 function subscales: affect regulation, interpersonal boundaries, self-punishment, self-care, anti-dissociation/feeling-generation, anti-suicide, sensation-seeking, peer-bonding, interpersonal influence, toughness, marking distress, revenge and autonomy. Healthcare use will assess the type and frequency of healthcare use over the previous 3-month period. The BA-SSI completion item will ask participants to estimate how much of the SSI they completed, on a sliding scale from 0 to 100.

### Sample size

A previous randomised controlled trial completed at FUSED showed that less motivated clients receiving CBT augmented with a small amount of motivational content had significantly better outcomes at 1-month follow-up than those who did not receive this content.^25^ At 3-month follow-up, a between-group effect size (Cohen’s d) benefit persisted of 0.37 (−0.20 to 0.93). Based on a power of 0.80, alpha of 0.05, assuming a correlation of 0.50 between baseline and post-training assessments, a small between-group effect size d=0.35 and 10% attrition between each of the 5 waves of data collection (40% attrition in total), we will be required to randomise 162 participants to CBT-TA and 68 participants to CBT-T (n=230).^44^ Over previous trials, around 50 clients have completed treatment at FUSED annually. To ensure we can randomise 230 clients over 4 years, we will open referrals to people with binge eating disorder (previously not eligible for a service), add four registered clinical psychologists who will have an ongoing client load of 2–5 people to the usual staffing of clinical psychology postgraduate trainees, and advertise the service.

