Third, acute augmentation (defined as interventions delivered immediately before, during or after a session of manualised psychological therapy with the aim of enhancing the impact of the therapy, either as a single intervention or across multiple therapy sessions) of ED treatment has also been shown to significantly improve outcomes over therapy alone with no augmentation.^19^ These acute augmentations are designed to be delivered on at least one occasion and can be repeated but are not offered concurrently over the whole of the treatment duration.

Currently, only five trials in ED exist that use stratified treatment for gradual responders.^15^ To date, none have built in participant choice for personalisation of treatment. This collaborative decision-making is recommended in clinical practice for EDs,^20^ but no rigorous evaluation exists of this practice. We describe a CBT-T treatment protocol designed to reduce the outcome gap between rapid and gradual responders compared with our previous three evaluations of CBT-T.^15^ This augmented treatment, CBT-TA, differs from CBT-T in four main ways: (1) while the first three sessions of the two treatments do not differ, we will now use an a priori indicator based on the global EDE-Q score to differentiate rapid (EDE-Q ≥1.13) and gradual (EDE-Q <1.13) responders before the start of session 4; (2) in the CBT-TA group, gradual responders will have a collaborative discussion with the therapist as to the barriers to more rapid change; (3) these barriers will be matched to nine possible treatment augmentations, identified by a Delphi consensus study across four different panels: people with lived experience, significant others, clinicians and researchers; requiring 80% of participants from all four panels to rate a statement as either ‘Essential’ or ‘Important’ for the statement to be endorsed;^21^ and (4) the gradual responders will receive their choice from nine augmentations, which will be tackled within sessions in addition to treatment as usual over the next five sessions of therapy. In the CBT-TA group, rapid responders will be given access to the platform housing the augmentations, but this content will not be discussed in therapy.

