This protocol is reported following Standard Protocol Items: Recommendations for Interventional Trials guidelines.^22^ The overall aim of this randomised controlled trial is to evaluate the comparative effectiveness and acceptability of CBT-T for non-underweight clients with EDs aged 15 years and above to CBT-TA. To achieve this, participants will be randomised to either receive CBT-T or CBT-TA. Our first specific aim is to examine superiority of CBT-TA (in clinically determined gradual responders) against a CBT-T control group. The secondary research aim is to examine superiority of CBT-TA (in clinically determined rapid responders) against a CBT-T control group. We also will address an exploratory aim, namely, whether any differences exist between CBT-TA (passive augmentation) in clinically determined rapid responders vs CBT-TA (active augmentation) clinically determined gradual responders.

First, we hypothesise that gradual responders in CBT-TA will have significantly lower ED psychopathology compared with gradual responders in CBT-T at end of treatment and that these gains will be maintained at the 3-month and 6-month follow-up. We also hypothesise that remission will be higher in the former than latter group. Second, we hypothesise the same advantages for the rapid responder group in CBT-TA over rapid responders in CBT-T. We will also explore (1) change in health service utilisation including primary, secondary and tertiary care, (2) engagement and completion data between the two conditions to establish the relative acceptability of the interventions, and (3) client’s experiences of therapy in the form of qualitative feedback.

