Analyses will be undertaken with a treatment-policy approach (ie, intention-to-treat) and will include all participants in the group to which they were randomised, regardless of actual receipt or uptake of the intervention or withdrawal from the study (ICH E9 R1^45^). Mixed-model repeated measures analysis will be used for the continuously scaled primary outcome and secondary outcome variables. An unstructured residual variance-covariance matrix will accommodate within-participant dependency. The model will include factors of study condition (CBT-T, CBT-TA), occasion of measurement (baseline, 4, 10, 22 and 34 weeks post-randomisation) and their interaction as fixed effects, with a random intercept to account for variation between individual participants. The primary outcome will be assessed by a planned comparison of the difference between groups in change of the primary outcome variables over time. Given the assumption of MRMM that data are missing at random (MAR), multiple imputation will be used to replace missing observations. To examine robustness of the results and the MAR assumption, sensitivity analyses will be conducted using the tipping point and delta adjustment method. Additionally, we will run a number needed to treat analysis, based on the proportion of participants in each arm who meet the prespecified criteria for remission,^46^ (i) global EDE-Q score ≤2.77, (ii) BMI ≥18.5 and (iii) no ED behaviours in the previous 1 month period.

Analyses of secondary outcome variables will follow the same methods as the primary outcome except for the behavioural count variables, which will be analysed with generalised linear mixed modelling (GLMM). Separate GLMM models with a log link function and gamma distribution will be used to account for the right skewed health utilisation data.

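### The stated 80% power for 162 v 68 does not hold for the planned difference in change at end of treatment with the stated attrition; there it is about 61%, or 71–72% with equal baseline means

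*Protocol article*

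**What the plan says.** The Sample size section lists its inputs: "Based on a power of 0.80, alpha of 0.05", then "assuming a correlation of 0.50 between baseline and post-training assessments", and "a small between-group effect size d=0.35 and 10% attrition between each of the 5 waves of data collection (40% attrition in total"). It concludes "we will be required to randomise 162 participants to CBT-TA and 68 participants to CBT-T (n=230"). It cites a reference but names neither a formula nor a contrast.

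The analysis section describes a mixed model with condition, five occasions (baseline and weeks 4, 10, 22 and 34) and their interaction. Its primary test is: "The primary outcome will be assessed by a planned comparison of the difference between groups in change of the primary outcome variables over time". No single time point is fixed there. The Introduction places the first hypothesis in time: "gradual responders in CBT-TA will have significantly lower ED psychopathology compared with gradual responders in CBT-T at end of treatment", with the gains expected to persist at the two follow-ups.

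On when the arms can diverge, the Introduction says "while the first three sessions of the two treatments do not differ". The Randomisation and blinding section keeps participants and therapists blinded up to session 4, and the Study design section places T2 immediately before session 4.

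**The concern.** A power figure belongs to a particular contrast. T1 precedes randomisation and T2 precedes any augmentation, so the treatment can have no effect at two of the five waves. A calculation that credits those waves with the full d=0.35, or that omits dropout, gives more power than a test of change from baseline to end of treatment.

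If the 80% does not belong to the planned test, a true d=0.35 at T3 would be missed about four times in ten rather than two. A null result could then be read as evidence of no benefit. Any recalculation for gradual responders that starts from the same formula would carry the overstatement with it.

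**Working it through.** **Inputs.** From the Sample size section: d=0.35 (SD 1), r=0.50, alpha 0.05, power 0.80, 10% loss per gap, 162 v 68. From the Randomisation and blinding section: ratio 2.4:1 and 42% gradual responders (1/0.42 = 2.38). Assumed here: two-sided test, r=0.5 between every pair of waves (compound symmetry), monotone dropout, normal approximation. Retention over T1–T5 is taken two ways: 1, 0.9, 0.8, 0.7, 0.6 (40% total), or 0.9 compounded over four gaps (34.4% total).

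**Step 1: reproduce the stated N.** With k the ratio and V a variance factor,

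n(CBT-T) = (1 + 1/k)(1.96 + 0.8416)² V / 0.35².

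- *Constant difference averaged over five waves.* V = (1 + 4×0.5)/5 = 0.60. Dividing by mean retention 0.80 gives 0.75. With k=2.38: 68.2 v 162.5.
- *Same average, compounded loss entering wave by wave.* V = 0.7455. With k=2.4: 67.7 v 162.4. The additive 40% loss entered this way gives 69.8 v 167.6.
- *Single time point, baseline-adjusted, no attrition.* V = 1 − 0.5² = 0.75. With k=2.38: again 68.2 v 162.5.

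The first and third coincide because 0.60/0.80 = 1 − 0.5² = 0.75. Applying the full 40% loss to the third raises the CBT-T arm to about 114 (68.2/0.6), so that route fits the printed N only if attrition is omitted.

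**Step 2: power of the planned contrast.** The model has separate arm means at each occasion, a difference of 0 at T1 and T2 and 0.35 at T3–T5. V is the variance factor of the contrast from the generalised least squares information under dropout, and

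power = Φ(0.35 / √[V(1/162 + 1/68)] − 1.96), with 1/162 + 1/68 = 0.02088.

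- T1 to T3, free baseline, 40% loss: V = 1.176, SE = 0.157, 0.35/SE = 2.23, power 60.8%. With compounded loss: V = 1.166, power 61.2%.
- T3, baseline means constrained equal: V = 0.926 and 0.916, SE = 0.139 and 0.138, power 71.1% and 71.6%.

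| Contrast, all randomised, stated attrition | Power |
|---|---|
| T1 to T3, free baseline | 61% |
| T1 to T4, free baseline | 57–58% |
| T1 to T5, free baseline | 53–55% |
| T3, equal baseline means | 71–72% |
| T3, equal means at T1 and T2 | 76% |
| Mean of T2–T5 minus T1 (no effect at T2) | 57–58% |
| Mean of T3–T5 minus T1, free baseline | 77–78% |
| Mean of T3–T5, equal baseline means | 90–91% |
| Mean of T3–T5 minus mean of T1–T2 | 91% |

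**Step 3: sensitivity.** With no dropout at all, T3 power is 67.8% (free baseline) or 79.9% (equal baseline means). With 34.4% attrition, T1-to-T3 power runs from 54% at r=0.4 to 82% at r=0.7.

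**Step 4: gradual responders.** 162×0.42 = 68 and 68×0.42 = 28.6, about 29. With 1/68 + 1/29 = 0.04919 and the same V, T3 power is 31% (free baseline) or 37–38% (equal baseline means). This assumes that the same d, SD and r hold in that subset.

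**The case against.** Four points deserve weight.

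1. *The origin of the N is unknown.* A reader might infer that 162 v 68 was derived from the five-wave average. The article does not say so. The wording about a baseline to post-training correlation suits the baseline-adjusted single-time calculation at least as well. The ratio also allows a third idea: 162×0.42 = 68 hints at 68 as a per-group target, though no equal-allocation formula tried gave exactly 68. This objection stands. Only a match can be claimed, and on either matching route the result is not the planned end-of-treatment contrast with attrition.

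2. *The contrast is open.* The analysis section does not tie the primary test to T3, and the hypothesis also mentions the follow-ups. Contrasts averaging T3–T5 reach 90–91% if baseline means are constrained equal or T1 and T2 are averaged. So it would be wrong to say that no reading reaches 80%. Against this, the article describes no such constraint or averaging, and the hypothesis treats follow-up as maintenance of an end-of-treatment difference.

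3. *The 40% figure.* A reader might infer that it is an error for 34.4%. That is not supported: losing 10% of those randomised at each of four gaps totals 40%, and it reproduces 162 v 68 when mean retention is used. The article only needs to say which is meant.

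4. *The restriction to gradual responders costs more power.* True, and it is a separate matter. It does not repair the mismatch, which is present with all 230 included.

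**Conclusion.** The concern holds in limited form. The article states 80% power without naming what it is power for, and the figure is not delivered for the difference in change at end of treatment that its own hypothesis and analysis sections describe. With everyone randomised and the stated attrition, power at T3 is about 61% with a free baseline and 71–72% with baseline means constrained equal.

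These figures rest on d=0.35, r=0.5 between all waves, monotone dropout, and no effect at T1 or T2. The first is the protocol's own; r=0.5 is stated only for baseline with post-training and is extended here to all pairs; the last follows from the arms being the same before session 4. The shortfall is specific to contrasts at a single time point and shrinks or disappears for some averaged contrasts. The documents do not establish which formula was used, nor that 40% is a mistake.

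**What to change.** In the Sample size section:

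- Name the primary contrast (time point or average, and how baseline is handled) and the formula used.
- Set the expected difference to zero at T1 and T2, and apply attrition up to the time point tested.
- Restate the power that 162 v 68 gives. For T3 this is about 61%, or 71–72% with equal baseline means, at d=0.35 and r=0.5.
- Give the same calculation for the gradual responders whom hypothesis 1 compares: about 68 v 29, roughly 31–38% at T3.
- Say whether the 10% loss per gap is of those randomised (40% in total) or compounded (34.4%), and use one consistently.

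The analysis section should name the same contrast. If an average over T3–T5 is intended, saying so there settles most of the discrepancy for the full sample.

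The cost is one paragraph of recalculation and a less favourable stated power if T3 is the target. No extra participants, visits or data are proposed.

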### Recruitment

Participants will be recruited in South Australia between January 2025 and June 2028. Information about the study will be distributed to headspace centres (primary mental health services for youth), the Statewide Eating Disorder Service, and the Primary Healthcare Network that administers the National Eating Disorder Collaboration funded ‘Right Care Right Place’ co-ordination of ED referrals to Head to Health sites.

### Data collection, management and statistical analysis

Participant data will be collected on Qualtrics and securely stored on the Flinders University R drive and accessible only by the Flinders University research team. Participant names will be used to link surveys across assessment points and to usage data. Participant names will be deleted when data is downloaded from Qualtrics for analysis purposes and each participant will be assigned a randomly created user ID for deidentification purposes.

Interim analyses will be conducted to monitor the ratio of rapid responders vs gradual responders when 33% (n=48 in the active arm) and 66% (n=96 in the active arm) participants have completed session 4 (and therefore, have been categorised as rapid or gradual responders). Results from interim analyses will inform future randomisation ratios, with randomisation ratios being adapted if the proportion of rapid responders is ±10% of the assumed response rate of 58%. Results of interim analyses will be non-binding and subject to trial management group approval.

Analyses will be undertaken with a treatment-policy approach (ie, intention-to-treat) and will include all participants in the group to which they were randomised, regardless of actual receipt or uptake of the intervention or withdrawal from the study (ICH E9 R1^45^). Mixed-model repeated measures analysis will be used for the continuously scaled primary outcome and secondary outcome variables. An unstructured residual variance-covariance matrix will accommodate within-participant dependency. The model will include factors of study condition (CBT-T, CBT-TA), occasion of measurement (baseline, 4, 10, 22 and 34 weeks post-randomisation) and their interaction as fixed effects, with a random intercept to account for variation between individual participants. The primary outcome will be assessed by a planned comparison of the difference between groups in change of the primary outcome variables over time. Given the assumption of MRMM that data are missing at random (MAR), multiple imputation will be used to replace missing observations. To examine robustness of the results and the MAR assumption, sensitivity analyses will be conducted using the tipping point and delta adjustment method. Additionally, we will run a number needed to treat analysis, based on the proportion of participants in each arm who meet the prespecified criteria for remission,^46^ (i) global EDE-Q score ≤2.77, (ii) BMI ≥18.5 and (iii) no ED behaviours in the previous 1 month period.

Analyses of secondary outcome variables will follow the same methods as the primary outcome except for the behavioural count variables, which will be analysed with generalised linear mixed modelling (GLMM). Separate GLMM models with a log link function and gamma distribution will be used to account for the right skewed health utilisation data.

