## Methods and analysis

### Study design

The study is a parallel two-arm randomised controlled trial (see figure 1). Demographic data will be collected via the online referral then the full online assessment schedule will occur at baseline assessment (T1) which precedes face-to-face assessment with a therapist to finalise eligibility and desire to engage in CBT-T. Further evaluation of engagement and commitment to therapy will be conducted by asking clients to complete a behavioural activation single session intervention (BA-SSI) over the next 2-week period, at the end of which time (i) ED psychopathology will be assessed online again; (ii) level of engagement with the BA-SSI will be assessed; and (iii) randomisation will occur with the first therapy session occurring within a week. T2 will be conducted immediately preceding session 4, to inform extent of response. Assessments will be repeated at the end of treatment (T3) and 3-month and 6-month follow-up (T4 and T5). T3 will occur 10 weeks post-randomisation (12 weeks post-baseline). T4 and T5 will occur 22 and 34 weeks post-randomisation (24 and 36 weeks post-baseline respectively).

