### Study setting

The study will be conducted at the outpatient Flinders University Services for Eating Disorders (FUSED) in South Australia. Previous descriptions of four clinical trials from FUSED have been published,^23^,^26^ each including participants aged 15 years and above. The completer remission rate for CBT-T in our clinic is 36%,^15^ consistent with meta-analytic data for CBT for ED.^2^ In the current study, the CBT-T therapy will be conducted face-to-face by a mix of clinical psychology postgraduate trainees and registered clinical psychologists, under expert supervision. All data are self-reported and will be collected online via the Qualtrics survey platform. Participants can be self-referred or referred by a primary or mental health professional.

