### Eligibility criteria

Eligible participants (1) are aged 15 years and over; (2) have any DSM-5 diagnosis of ED as determined by the EDA-5 online clinical interview (https://eda5.org/) excluding anorexia nervosa and avoidant/restrictive feeding intake disorder for which no evidence of the efficacy of CBT-T exists; (3) consent to FUSED communicating regularly with their general practitioner; (4) reside in South Australia; and (5) can read independently at grade 2 level English. The age inclusion was informed by research^27^ showing that adolescents with an eating disorder and a mean age of 15 years self-select CBT rather than family-based treatment. Participants are not eligible if they report current life-threatening suicidal ideation, untreated psychosis, or substance dependence, or have a Body Mass Index (BMI)<18.5 (or BMI-for-age <5th percentile if an adolescent), or currently receiving a psychological therapy for an ED. Eligibility criteria will be assessed at the screening assessment and checked again in the face-to-face assessment.

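### Remission requires BMI of at least 18.5 for everyone, but adolescents enter on BMI-for-age, so an eligible adolescent below 18.5 cannot count as remitted while BMI stays there

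*Protocol article*

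**What the plan says.** Under Eligibility criteria, the age floor is set by "Eligible participants (1) are aged 15 years and over". The same section excludes people who "have a Body Mass Index (BMI)<18.5 (or BMI-for-age <5th percentile if an adolescent"). On its natural reading, the bracket replaces the adult threshold with an age-specific one for adolescents.

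Under Data collection, management and statistical analysis, remission has three parts, all required. The first is a global EDE-Q of 2.77 or less. The other two are "ii) BMI ≥18.5 and (iii) no ED behaviours in the previous 1 month period". No adolescent alternative is given for the weight part.

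Remission is used in two places. The analysis section says "we will run a number needed to treat analysis, based on the proportion of participants in each arm who meet the prespecified criteria for remission". The Introduction, for gradual responders in CBT-TA against those in CBT-T, says "We also hypothesise that remission will be higher in the former than latter group", and then hypothesises the same advantages for rapid responders.

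**The concern.** The trial is for people who are not underweight, and it uses two definitions of that state: one to let adolescents in and another to judge their outcome. Every adult enters already meeting the weight part of remission, so for adults it only guards against weight loss. For an adolescent who enters at or above the 5th percentile but below 18.5, the same line demands weight gain from someone the trial did not class as underweight. The endpoint then means different things at different ages.

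At stake are the remission comparisons and the NNT. Participants held out of remission by the weight line alone lower the remission rate in both arms, shrink the absolute difference and raise the NNT. In the smallest comparison group, gradual responders in CBT-T, a chance imbalance of one or two such adolescents would be visible.

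**Working it through.** **The two rules side by side, for an adolescent**

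| Position of the 5th percentile at that age | Entry rule | Remission rule | Result |
|---|---|---|---|
| Below 18.5 | BMI between the percentile and 18.5 is admitted | Same BMI fails | Not underweight at entry, yet not remitted while BMI stays there |
| Exactly 18.5 | Same threshold | Same threshold | Rules agree |
| Above 18.5 | BMI between 18.5 and the percentile is excluded | Same BMI passes | Someone who falls below the entry limit during the trial could still meet the weight part |

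The article gives no percentile values, so the row that applies cannot be read from it. The separate adolescent rule would have no purpose if the middle row held at every enrolled age. The rest of the working takes the first row.

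**Is the criterion out of reach?** The last assessment is late: "T4 and T5 will occur 22 and 34 weeks post-randomisation (24 and 36 weeks post-baseline respectively"). Weight gain needed = (18.5 − BMI) × height². At an assumed height of 1.65 m (height² = 2.7225):
- from BMI 18.4: 0.1 × 2.7225 = 0.3 kg
- from BMI 18.0: 0.5 × 2.7225 = 1.4 kg
- from BMI 17.0: 1.5 × 2.7225 = 4.1 kg

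Such changes are arithmetically possible within 34 weeks, so the criterion is not unreachable.

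**How many people?** The article states no adolescent share and no BMI distribution. Assume that 10–20% are under 18 and that 10–30% of those have BMI below 18.5. The planned numbers are given by "we will be required to randomise 162 participants to CBT-TA and 68 participants to CBT-T (n=230").
- Low: 230 × 0.10 × 0.10 = 2.3 people, or 1%
- High: 230 × 0.20 × 0.30 = 13.8 people, or 6%

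**Effect on the NNT.** Let f be the share in each arm who enter and stay below 18.5, and suppose they would otherwise remit at the same rate as everyone else. Each arm's rate is multiplied by (1 − f), so the NNT is multiplied by 1/(1 − f). For CBT-T, take the clinic's figure: "The completer remission rate for CBT-T in our clinic is 36" per cent. For CBT-TA, assume 46%. With no one affected, the NNT is 1/(0.46 − 0.36) = 10.0.

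| f | CBT-TA | CBT-T | Difference | NNT |
|---|---|---|---|---|
| 1% | 45.5% | 35.6% | 9.9 points | 10.1 |
| 2% | 45.1% | 35.3% | 9.8 points | 10.2 |
| 5% | 43.7% | 34.2% | 9.5 points | 10.5 |
| 6% | 43.2% | 33.8% | 9.4 points | 10.6 |

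**Weight of one person.** The NNT is described by arm. In CBT-T, one person is 1/68 = 1.5 points. The first remission hypothesis concerns gradual responders, assumed to be 42% (Randomisation and blinding): 68 × 0.42 = 28.6 people before attrition, so one person is at most 1/28.6 = 3.5 points. With f between 1% and 6%, that group would contain 0.3 to 1.7 affected adolescents.

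**The case against.** A reader might infer that these adolescents can never remit. The documents do not support that: BMI is not fixed, and the arithmetic above shows that 18.5 can be reached during follow-up. The accurate statement is that they cannot count as remitted while BMI is below 18.5.

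A reader might also take the 3.5-point figure as the error in the NNT. It is not. It applies only to the CBT-T gradual responders, whereas the NNT rests on the whole arm. It also assumes that the person would otherwise certainly have remitted; at the clinic's 36%, the expected shift per person is 0.36 × 3.5 = 1.3 points. Any one participant carries that weight in a group of 29, whatever the BMI rule.

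Further objections have force. The size of the affected group is unanchored: the trial excludes anorexia nervosa and underweight and opens referrals to binge eating disorder, so few adolescents may fall in the band. The expected effect is the same in both arms and does not change the direction of the difference. If the eligibility bracket were read as adding to the adult threshold and not replacing it, no adolescent would enter below 18.5, but that is not how it reads.

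Finally, the remission criteria come from a cited source, and applying them to minors might be left to a fuller document. This does not dispose of the point. The article states the criteria in full and calls them prespecified, so this is a stated rule that conflicts with another stated rule, not an omitted detail.

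**Conclusion.** The inconsistency is real and can be seen from the article alone: adolescents are judged by BMI-for-age at entry and by an absolute BMI of 18.5 at remission, and nothing reconciles the two. Where the 5th percentile lies below 18.5, the remission rule misclassifies some adolescents for as long as their BMI stays under that line.

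The effect is confined to the remission hypotheses and the NNT. The primary outcome, the EDE-Q global score, and the sample size are untouched. On the assumed 1–6% affected, the NNT moves from 10.0 to between 10.1 and 10.6. This rests on an assumed adolescent share, an assumed BMI distribution, an assumed 46% remission in CBT-TA, equal shares in both arms and no affected participant reaching 18.5. It is a modest defect, worth correcting because correction is nearly free and because changing a responder definition after outcome data have been seen would look data-driven.

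**What to change.** Reconcile the weight part of the remission definition with the entry rule, so that both use one definition of not underweight: the eligibility section's adult rule for adults and its BMI-for-age rule for adolescents.

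State in advance which rule applies to participants who turn 18 between entry and the 6-month follow-up. Classifying by age at entry and classifying by age at each assessment can give different answers for the same person, so one must be chosen and written down.

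Report remission and the NNT under the current BMI ≥18.5 rule as a sensitivity analysis, so that results can still be compared with earlier remission rates such as the clinic's 36%.

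The cost is a sentence or two of wording, settled before outcome data are examined, and one extra tabulation. Age is already collected, BMI is already needed for the remission definition, and the percentile rule is already applied at entry. The main analysis loses a little comparability with earlier rates, which the sensitivity analysis covers.
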